In order to consider how to determine the most sensitive and specific test for the symptoms of SRC, we propose that an interdisciplinary approach would be powerful in determining the levels of changes in the biological system, where the dynamics of change are consistently present. Changes in cognitive, visual, and movement functions are symptoms of SRC, and it has been suggested that the multimodal assessment of these has better sensitivity than balance or cognitive tests alone [52]. For example, based on elements of the SCAT5, short-term memory, balance, and symptom severity are rated. However, while the test-retest reliability of the SCAT5 as a whole is reported to be moderate to high, the reliability coefficients of SAC and mBESS (rs = 0.58 and 0.40, respectively) are low [53]. Partly, this is suggested to be due to individual variability and the interval-scale scores of the tests. However, currently, there are no quantitative tests for cognitive, visual, or movement function included in the SCAT5, which limits the generation of precise numerical values that can be used to identify and characterize symptoms of SRC.

Executive function has been examined in line with neurological conditions [54] and is relevant to the study of acute and chronic effects of head trauma [55,56,57]. Executive function and its relationship with decision making based on specific environmental cues that underpin motor behaviors are key in sports performance and injury risk. Evidence linking concussive events to future concussive events [58] and twice the likelihood of obtaining another musculoskeletal injury [59] suggests that executive function and aspects of neuromuscular and movement functions are impaired after concussive incidents. However, there is a need to study the acute and chronic effects of mTBI/SRC individually, as well as holistic measures of body movement and coordination, to facilitate the identification of the most sensitive and specific indicators of injury and brain function.

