In order to understand the facets of motor control function that may underpin changes in the performance of gross motor skills, it is important to perform a number of tests of executive function and specific aspects of perception-action coupling. For example, reaction time is a promising indicator of visuo-motor deficits following SRC [65], which is quick and easy to quantify. Finger-tapping and fine motor skill tasks (f/e the Perdue Pegboard test) [66,67,68,69] have been used widely in cognitive psychology to identify neurological conditions. In order to understand the facets of motor control function that may underpin changes in the performance of gross motor skills, we will perform a number of perception-action and physical tasks. Specifically, we will explore reaction time, executive function (Stroop word test), and fine motor skills (finger tapping and Perdue Pegboard).

The study’s aim, therefore, is (1) to examine changes in biomarker concentrations and biomechanical and cognitive-motor abilities of elite rugby players across three-match tournaments until 72 h after the final game and (2) to explore the relationship between subconcussive head impacts and their intensity and changes in blood biomarker concentrations, biomechanical tasks, and cognitive-motor tasks.

It is hypothesized that (1) the whole-body movement, coordination, and cognitive-motor tasks will decrease significantly with the duration of games played because of fatigue and/or concussive events; (2) blood biomarkers (i.e., CK, cardiac troponin T, NSE, S100B, BDNF, GFAP, and UCHL1) will increase significantly after rugby tournaments; (3) a correlation will be explored between the number of head impacts (quantified with a notational analysis) and the aforementioned indicators. The study has been registered as a clinical trial (clinicaltrials.gov NCT04841876 (assessed on 16 March 2022)) and has been approved by the Research Ethics Committee of Hong Kong Baptist University (REC/20-21/0452).

All data collection, including motor control, biomechanics, and blood analyses, will be performed through formal collaboration with the universities constituting the Sport and Health Interdisciplinary Group in Movement & Performance from Acute & Chronic Head Trauma (IMPACT) research group based at Cardiff Metropolitan University. Funding for this project will be covered by the institutes involved.

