Finger-to-nose: A finger-to-nose task will be performed within the data-capturing area in accordance with a modified SCAT 5 procedure, with the subject standing with both feet on the force plate. “I’m going to put your coordination to the test right now. Stand on both feet, eyes open, and your dominant arm extended in front of you. Perform five sequential finger-to-nose repetitions, touching the tip of the nose with your index finger on the start signal, then returning to the starting position. Execute the actions as quickly and properly as possible”. Cognitive-motor tasks are covered in Section 2.3.2.

Prior to the cognitive-motor exam, participants will take the Mini-Mental State Examination (MMSE), which consists of 30 questions that assess participants’ sense of orientation, attention, immediate and delayed recollection, language, and construction [75,76].

In order to examine cognitive function, a series of tasks will be performed (i. Pegboard; ii. Tapping Task; iii. Stroop word test; iv. reaction time task; v. working memory).

Purdue Pegboard: The Purdue Pegboard is used to explore bimanual finger and hand dexterity [66,67]. The Purdue Pegboard consists of two parallel rows of 25 holes, with pegs first inserted into two laterally positioned cups, followed by collars and washers first pushed into two central cups. Four subtests are performed. The first subtest entails placing as many pins as possible in the holes (from top to bottom) within a 30 s time constraint, first with the favored hand, then with the non-preferred hand, and finally with both hands. In the fourth subtest, the individual alternates between using both hands to construct “assemblies” of a peg, a washer, a collar, and another washer in 1 min.

Tapping Task: The finger-tapping test (FTT) is a lateralized coordination and motor speed test. To conduct the test, the palm will be taped to a flat board with fingers splayed. The index finger will then “tap” on a computer keyboard button. Participants will be instructed to tap each finger on the button as quickly as possible throughout a 10 s period. There will be three trials with each finger.

To increase the number on the counting device with each tap, the number of taps will be averaged over trials [77].

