Stroop word test: The Stroop color test will be carried out on a computer with the help of the online demo test [78]. Participants will be seated comfortably at the computer workstation and will be instructed on how to conduct the test. The test will be a demonstration and take 2 min to complete. Participants will be required to say the words aloud, since verbal and cognitive performance has been reportedly related to mild concussion symptoms. Stroop will be run using both vocal and keyboard responses. The four colors red, blue, green, and yellow will be utilized to convey 40 words for 2 s each. To allow scoring after the test, a screen + camera capture of the Stroop word and the participant response will be used for the spoken response. The view of the video will include the participant and the Stroop word on the screen. In the keyboard response task, participants will respond to the four colors using the r, b, g, and y keys on the keyboard. We will then explore whether there is a correlation between keyboard and verbal scores and if one of these modes of answering is more affected by a blow to the head.

Reaction time task: To quantify reaction time, a computerized reaction time test will be performed. The test will be repeated 5 times with each hand; more information on the reaction time challenge may be found here [79].

Working memory: In the Digit Span Backward test, participants are shown a string of digits that must be repeated backward. According to the SCAT 5, the working memory score is determined from the temporal reactions to rising number strings [53]. The raw data will be used to calculate working memory.

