#### 2.4.2. Cognitive-Motor Tasks

The cognitive-motor tasks will be examined using the standard clinical procedure. Specifically, Stroop word test: Scores will be reported as the average response time in incompatible trials minus compatible trials. Reaction time task: The task will be scored digitally in milliseconds. Purdue Pegboard: The number of pins inserted in the time period for each hand determines the score for the pin (peg) insertion subtests. The total number of pairs of pins inserted determines the score for the bimanual condition. The assembly score is the number of components assembled (for more information on how to set up/run a test, check the extended usage instructions in the Scoring Application or on our website). Finally, Tapping Task: Timing, consistency, and frequency will be quantified.

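### The backward digit-span score is stated in terms of time, with no term for correct recall, so a loss of span can go unseen or, under some timing rules, look like faster responding

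*Protocol article*

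**What the plan says.** The working-memory paragraph of section 2.3.1 names the Digit Span Backward test and describes the task: "participants are shown a string of digits that must be repeated backward". The next sentence refers to the SCAT5, with a citation, and gives the score: "the working memory score is determined from the temporal reactions to rising number strings". The paragraph ends with "The raw data will be used to calculate working memory". It does not mention correct answers, longest string, handling of errors, a stopping rule or the direction of the score.

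Section 2.4.2 opens with "The cognitive-motor tasks will be examined using the standard clinical procedure". It then sets out scores for the Stroop test, reaction time, Pegboard and tapping, but not for working memory.

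Working memory is the last of the five cognitive tasks listed in section 2.3.1 ("iv. reaction time task; v. working memory"). Table 1 schedules it at baseline, after each of the three games, and at 24, 48 and 72 h after the third. The first hypothesis in the Introduction is that "the whole-body movement, coordination, and cognitive-motor tasks will decrease significantly with the duration of games played".

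**The concern.** The task and its score do not match. The task succeeds or fails on whether the string is reversed correctly, and on the length at which this breaks down. The stated score rests on timing. Two problems follow if the sentence is applied as written.

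- **Errors are not penalised.** A quick wrong answer scores the same as a quick right one.
- **The mix of strings can differ between sessions.** Longer strings take longer to repeat. If testing stops when a player fails, a player whose span has shrunk is timed on shorter strings, and his average time can fall.

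The hypothesis predicts decline. A score that can miss a decline, or in some configurations reverse it, works against the test of that hypothesis. It also mixes memory with speaking speed and with any shift between speed and accuracy after exertion. That matters here because the Introduction argues that exercise already confounds concussion measures.

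**Working it through.** The article states no figure for this outcome, so there is nothing to reproduce. The check has two parts.

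**1. Does anything in the article supply a correctness term?**

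- The closing sentence of the working-memory paragraph says only that raw data will be used. It adds no rule.
- The general sentence at the start of section 2.4.2 points to standard clinical procedure. It does not override section 2.3.1, which presents timing as the SCAT5 rule.
- The Introduction says that "currently, there are no quantitative tests for cognitive, visual, or movement function included in the SCAT5". This sits awkwardly with a timed SCAT5 working-memory score, but it does not settle what was meant.
- Table 1 and the Discussion give no scoring.

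The timing rule is therefore the only specific working-memory score in the article.

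**2. What could the timing rule do?** Every value below is assumed; none comes from the article.

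- Response time for a string of L digits: t(L) = a + b × L.
- Score: mean t(L) over the strings that are timed.
- Before the match: lengths 3, 4, 5 and 6, mean length 4.5.
- After the match: span falls to 4 and testing stops at the first failure, at length 5.
  - Failed string timed: lengths 3, 4, 5, mean length 4.
  - Correct strings only: lengths 3, 4, mean length 3.5.

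| a, b (s) | Before: a + 4.5b | After, failed string timed: a + 4b | After, correct only: a + 3.5b |
|---|---|---|---|
| 1.0, 0.6 | 3.7 | 3.4 (-8%) | 3.1 (-16%) |
| 0.8, 0.4 | 2.6 | 2.4 (-8%) | 2.2 (-15%) |
| 1.5, 0.8 | 5.1 | 4.7 (-8%) | 4.3 (-16%) |

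General slowing that cancels the change is (before / after) - 1:

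- Failed string timed: 3.7/3.4 gives 8.8%, 2.6/2.4 gives 8.3%, 5.1/4.7 gives 8.5%.
- Correct only: 3.7/3.1 gives 19.4%, 2.6/2.2 gives 18.2%, 5.1/4.3 gives 18.6%.

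With 10% slowing the two variants disagree in sign. For a = 1.0 and b = 0.6, timing the failed string gives 3.4 × 1.1 = 3.74 s (+1%), and timing correct strings only gives 3.1 × 1.1 = 3.41 s (-8%).

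A steeper cost per digit (a = 1.0, b = 1.0) gives 5.50 s before and 5.00 s (-9%) or 4.50 s (-18%) after. The break-even points are then 10% and 22%.

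**No stopping rule.** Now all four lengths are always given, lengths 5 and 6 are answered wrongly after the match, and a wrong answer takes f times the usual time. With a = b = 1.0 the usual times are 4, 5, 6 and 7 s, mean 5.50 s.

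- f = 0.5: (4 + 5 + 3 + 3.5)/4 = 3.88 s, apparently faster.
- f = 0.75: (4 + 5 + 4.5 + 5.25)/4 = 4.69 s, apparently faster.
- f = 1: 5.50 s, no change; the lost span is invisible.
- f = 1.25: (4 + 5 + 7.5 + 8.75)/4 = 6.31 s, apparently slower.

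The same loss of span can therefore appear as faster, unchanged or slower responding, depending on rules that the sentence does not contain.

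**The case against.** The strongest reply is that the sentence reports, perhaps loosely, how an existing instrument is scored. Temporal reactions is not defined, raw data are to be kept, and section 2.4.2 invokes standard clinical procedure. The authors may well intend a correctness-based score. This stands as a caution about intent. It does not rescue the sentence, which would then misdescribe the score and need the same correction. How the SCAT5 actually scores the test cannot be settled from the article, and the point does not depend on it.

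A second reply is that an article may leave scoring detail to the full protocol. That is fair for the absence of a working-memory entry in section 2.4.2, which alone would be no finding. But section 2.3.1 does not leave the score open; it states one.

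A third reply is that averaging over strings, the stopping rule and the linear time model are all assumed. This stands in full. A reader might infer that a player who loses span will generally appear improved, by about 16%, and that slowing must reach about 20% before any worsening shows. The article does not support that. Those figures need the failed string to be left out of the average. Timing it halves the effect and brings the break-even down to about 9%, and slow wrong answers give worsening. Comparing times at the same string length, which the article does not exclude, would remove the string-mix problem, though not the scoring of wrong answers.

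Finally, the reach is small. The sample size rests on blood biomarkers, and the Discussion's list of cognitive tests expected to decline names four tasks and not this one, although the list is introduced as non-exhaustive.

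**Conclusion.** The point holds in a limited form. The article pairs a test of correct backward recall with a time-based score that has no term for correctness or length reached, and nothing elsewhere in it corrects this. That conclusion rests on the text alone.

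The size is illustrative. Under the three main assumed timing pairs, a fall in span from 6 to 4 changes mean time by about -8% (failed string timed) or about -16% (correct strings only). Slowing of about 9% and just under 20%, respectively, cancels this. With no stopping rule the result can go either way or show nothing. What is established is that the rule as written can miss or mask a loss of span; that it would invert one is possible but not shown.

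The consequence is confined to one of five cognitive tasks. It is worth correcting before data collection but does not threaten the trial as a whole.

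**What to change.** Replace the scoring sentence in section 2.3.1 with: *The working memory score is the number of strings correctly repeated backward (or the longest string correctly reversed). Response time, if used, is secondary, computed on correct responses only and compared at the same string length.* Choose one of the two accuracy scores, and add it to section 2.4.2 beside the other cognitive-motor scores.

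The cost is wording only, provided that the correctness of each response is recorded, which the task yields anyway. The one downside is that an accuracy score has few steps and so is coarser than a time.

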#### 2.3.2. Sports Performance Analysis

Sports performance analysis of training games will occur via computerized observation using a HUDL Elite software package (Version 11, SportsCode, Warriewood, NSW, Australia). This software will be used to create a workflow analyzing tactical and physical elements of performance, including collisions, impacts, and bouts of high-speed running (HSR). Collision measurement will occur after sessions and will be undertaken by two experienced performance analysts. The collision count will be deemed to include the sum count of all ball carries into contact, rucks, mauls, and, most importantly, tackles. All sessions will be recorded using a digital camera system.

Evidence-based preparation in elite rugby union has led to the increasing use of athlete tracking. External loads generated by the players will be calculated using accelerometers, local positioning systems (LPSs), global positioning systems (GPSs), and optical tracking systems [80]. Body load and impact measurements can be used to quantify the amount and intensity of any physical encounters and collisions between athletes, objects, or surfaces. Any serious injuries to the players during the three-game period will be managed immediately by the medical team.

Each player will wear a GPS micro-technology unit (mass = 67 g, 10 Hz V5.0 and 10 Hz S5, Catapult Innovations, Scoresby, VIC, Australia) in a pocket fitted in his/her playing jersey on the upper thoracic spine between the scapulae. Each GPS unit collects data at a rate of 10 hertz. The dependability of the device has already been proven to be valid and reliable for measuring speed and distance in team sports [81].

Because of their training and competitive routines, all players are completely familiar with the units. Throughout the data-collecting period, each player will wear the same assigned GPS unit. To ensure a comprehensive and high-quality satellite signal, GPS units will be turned on at least 10 min before the game. After the game, GPS data will be downloaded to a laptop and analyzed using Sprint 5.1 software (Catapult Innovations, Scoresby, VIC, Australia). Body load (measured in G-force) is the sum of all forces applied to an athlete, including acceleration/deceleration, related changes in direction, and impacts from both player-to-player and ground contact (foot strikes and falls) (Table 2).

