We expect a decline in coordination, cognitive-motor tasks, and whole-body mobility, owing to exhaustion and/or concussions, as the number of games increases. Concussive events and injuries will be assessed using a notational analysis recorded during each match. Specifically, a reduction in the performance variable associated with the mBESS stance and finger-to-nose task is expected. In the analysis of the emergent coordinative structures of the passing task, we expect to show a shift to a critical level, before which the outcome variable of passing accuracy will be maintained. Past this critical point, the self-organization of the biological structures will be unable to remain stable, and the coordination variability will rise above the functional level. Examining the structure and timing of these movement characteristics will allow us to link the dynamics to the evolving rugby games. Cognitive function tests, including the Pegboard, Tapping Task, Stroop word test, and reaction time task, are expected to display a reduction in outcomes in the repeated testing sessions as a result of fatigue and/or a concussive event. With respect to the blood-based biomarkers, we expect CK, cardiac troponin T, NSE, S100B, BDNF, GFAP, and UCHL1 to increase after a rugby match, as exercise and contact sports have been shown to cause these biomarkers to increase [8,9,10,11,12,13,14,15,16,17,18,19,20,21,22,23,24,25,26,27,28,35,37,44,45,46,47,48,49]. However, cortisol concentrations may not increase, as cortisol has been shown not to increase after American football play in the absence of brain injury [10,37]. Some variations in biomarker concentrations in the blood are expected to correspond to changes in biomechanical and cognitive-motor activities. In the examination of the interaction of whole-body movement, coordination testing, cognitive-motor tasks, and blood-based biomarkers, we expect to observe those variables most related to changes in the testing session and the other outcome variables, including the accuracy of passing.

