	**Notational Analysis**	**Notational Analysis**	**Notational Analysis**
	Performance related analysis: to include X, Y, Z	Performance related analysis: to include X, Y, Z	Performance related analysis: to include X, Y, Z

**Table 2 biology-12-01089-t002:** Adapted from Gabbett (2013) [82], zones used to study “impacts” during rugby games 1–3.

Zone	Gravitational Force	Description of Impact
**1**	<5.0–6.0	Very light impact, hard acceleration/deceleration/change of direction while running
**2**	6.1–6.5	Light to moderate impact, minor collision with opposition player, contact with ground
**3**	6.5–7.0	Moderate to heavy impact, making tackle or being tackled at moderate velocity
**4**	7.1–8.0	Heavy impact, high-intensity collision with opposition player/s, making direct front on tackle on opponent traveling at moderate velocity, being tackled by multiple opposition players when running at submaximal velocity
**5**	8.1–10.0	Very heavy impact, high-intensity collision with opposition player/s, making direct front on tackle on opponent traveling at moderate velocity, being tackled by multiple opposition players when running at near maximal velocity
**6**	>10.1	Severe impact, high-intensity collision with opposition player/s, making direct front on tackle on opponent traveling at moderate velocity, being tackled by multiple opposition players when running at maximal velocity

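### Aim 2 and hypothesis 3 concern the number and intensity of head impacts, but no measure the protocol describes captures either one

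*Protocol article*

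**What the plan says.** The Introduction gives the second of two study aims as "to explore the relationship between subconcussive head impacts and their intensity and changes in blood biomarker concentrations, biomechanical tasks, and cognitive-motor tasks". Hypothesis 3 then names the source of the count: "a correlation will be explored between the number of head impacts (quantified with a notational analysis) and the aforementioned indicators".

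Section 2.3.2 describes the notational analysis. Two performance analysts work from recorded video, and the rule for the count is: "The collision count will be deemed to include the sum count of all ball carries into contact, rucks, mauls, and, most importantly, tackles". The workflow is also said to cover impacts and high-speed running, as items beside collisions. Impacts are not defined there and are not tied to the head.

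The same section describes a GPS unit worn "in a pocket fitted in his/her playing jersey on the upper thoracic spine between the scapulae". Its output is defined as follows: "Body load (measured in G-force) is the sum of all forces applied to an athlete, including acceleration/deceleration, related changes in direction". The sentence goes on to include player-to-player and ground contact, with foot strikes and falls among the latter. Table 2 sorts these forces into six zones, the lowest of which covers hard acceleration, braking and turning while running.

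Table 1, in its notational analysis rows, gives only "Performance related analysis: to include X, Y, Z". The Discussion assigns the notational analysis a further task: "Concussive events and injuries will be assessed using a notational analysis recorded during each match".

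**The concern.** The exposure named in the aim is not the exposure defined in the methods. A carry, ruck, maul or tackle may or may not involve the head. Body load rises with running, turning and landing as well as with contact.

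This matters particularly here because of what the study is trying to separate. The Introduction says that S100B is also present in skeletal muscle and is confounded by exercise, and that creatine kinase is measured to help identify the muscle source. Collision count and body load plausibly follow the same muscular work and trauma. A correlation between collisions and S100B could therefore be written up as a head-impact relation when it reflects work rate. Conversely, if head impacts do drive a marker, a count made up mostly of contacts that spare the head would blur the relation.

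Other parts of the protocol rely on the same variable. The Stroop paragraph plans to ask which response mode is more affected by a blow to the head. The Abstract and the Discussion promise data on how often head trauma events occur.

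**Working it through.** The protocol gives no figure for this point, so the main check is to compare the exposure named with the measures described.

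| Needed for Aim 2 and hypothesis 3 | Described in the protocol | Match? |
|---|---|---|
| Number of head impacts, by notational analysis (Introduction) | Sum of carries into contact, rucks, mauls and tackles (2.3.2) | No: all contacts, no head category |
| Same | An item called impacts (2.3.2) | Cannot be told: no definition, no mention of the head |
| Same | Notational variables in Table 1 | Cannot be told: placeholder only |
| Same | Concussive events and injuries from notational analysis (Discussion) | No: a different event from a subconcussive impact, and no coding rule |
| Intensity of head impacts | Body load and Table 2 zones from the trunk-worn unit | No: whole-body force; Zone 1 includes running without contact, Zone 2 includes contact with the ground |

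No row supplies a head-specific count or a head-specific intensity.

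**Can the consequence be sized?** Let C be the collision count, H the true head-impact count and M a marker, all standardised. Write M = βH + γC + error, where γ is any effect of work rate or whole-body contact that does not pass through the head. Then

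corr(C, M) = β × corr(C, H) + γ.

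*Case 1, γ = 0 (collisions act only through head impacts).* The relation is diluted: observed r = true r × corr(C, H). The following inputs are assumptions and none is in the protocol: true r = 0.60, corr(C, H) from 0.3 to 0.7, and one pair of values for each of the 20 sport-group players.

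- Observed r: 0.60 × 0.3 = 0.18, and 0.60 × 0.7 = 0.42.
- Fisher z, two-sided 0.05, both tails counted: power = Φ(atanh(r)·√17 − 1.96) + Φ(−atanh(r)·√17 − 1.96).
- r = 0.60: atanh = 0.693, × √17 = 2.86, power about 82%.
- r = 0.42: atanh = 0.448, × √17 = 1.85, power about 45%.
- r = 0.18: atanh = 0.182, × √17 = 0.75, power about 12%.

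A second assumed model takes 30 collisions per player, a between-player coefficient of variation of 0.3 to 0.5, and a fraction p of collisions (0.02 to 0.20) involving the head, with head impacts binomial given collisions. With v = (30 × CV)², corr(C, H) = p·v / √(v·[p²v + p(1 − p)·30]). This runs from 0.23 (CV 0.3, p 0.02) to 0.81 (CV 0.5, p 0.20). Observed r is then 0.14 to 0.48, and power about 9% to 59%.

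*Case 2, β = 0 and γ > 0 (no head effect, some work-rate effect).* Then corr(C, M) = γ. The correlation is not diluted at all; it is spurious as a head-impact relation.

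The two cases pull in opposite directions, and the protocol gives no value for β, γ or corr(C, H). The Case 1 figures show only how wide the answer is under assumption; they do not estimate what this study will lose.

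**The case against.** A reader might infer that head impacts will never be measured. The text does not go that far. Hypothesis 3 says that the notational analysis quantifies them, Section 2.3.2 lists impacts separately from collisions in a list that need not be complete, and all sessions are filmed, so analysts could code head contact. A video coding manual is also something an article may leave to a fuller document. All of this stands against the stronger reading. It does not remove the narrower point: the article defines the count and the load measure, and what it defines is not the exposure it names.

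It may also be said that the link between head-impact intensity and the trunk-worn unit is inferred. That is right: no sentence says that head-impact intensity comes from this unit. It is, however, the only source of impact intensity described, so the choice is between an unsuitable measure and none. Table 2 does allow running to be separated from contact zones, but those zones still grade whole-body force.

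Two further points stand. The power figures rest on assumed inputs, on single pairs from 20 players although data are taken after each of three matches, and on collisions acting only through the head, which the work-rate concern itself disputes. And both the aim and the hypothesis are worded as exploration.

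**Conclusion.** The point holds in this form: no measure described in the protocol captures the number or the intensity of head impacts, and the Introduction, Section 2.3.2, the Discussion and Tables 1 and 2 do not agree on what the notational analysis records. If the variables are used as described, whole-body contact and load would stand in for head impact. A reported relation could then reflect work rate, or a true one could be weakened. Neither the direction nor the size can be settled from the document, and the illustrative power figures should not be quoted as a property of the plan.

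The conclusion rests on the text alone and on no numerical assumption. It should be fixed, because one of the two stated aims has no matching exposure variable. It is not critical to the trial: the aim is exploratory, and Aim 1, hypotheses 1 and 2, the comparison of randomised groups and the sample size do not depend on it.

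**What to change.** 1. Add a direct head-contact code to the existing video workflow, counted per player and per match, with a written definition. If intensity stays in Aim 2, add a grade for it to the same code.
2. Have the two assigned analysts code it blind to biomarker and task results, and report their agreement.
3. Name this count as the exposure for Aim 2 and hypothesis 3, and replace the placeholder in Table 1 with the variables actually coded.
4. Label the collision count and GPS variables as whole-body contact and whole-body load, and do not count non-contact running (Zone 1) as impact. Removing Zone 1 does not make the remaining zones head-specific, so the label is needed as well.
5. If head contact or its intensity cannot be coded reliably, reword Aim 2, hypothesis 3 and the Discussion statement on concussive events to collisions and body load.

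The cost is extra coding time on video that will be recorded anyway, by analysts already assigned. Some head contacts will be obscured on video; their number, or the share of contacts that could not be judged, should be reported. Rewording alone costs nothing in data collection, but gives up the head-impact question.
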